## Abstract

**Background:**

Colorectal cancer (CRC) is the most common cancer in Europe with a mortality rate of almost 50%. The prognosis of patients is largely determined by the clinical and pathological stage at the time of diagnosis. Population screening has been shown to reduce CRC-related mortality rate. Most screening programs worldwide rely on fecal immunochemical testing (FIT). The effectiveness of a FIT screening program is not only influenced by initial participation rate, but also by program adherence during consecutive screening rounds. We aim to evaluate the participation rate in and yield of a third CRC screening round using FIT.

**Methods and design:**

Four years after the first screening round and two years after the second round, a total number of approximately 11,000 average risk individuals (50 to 75 years of age) will be invited to participate in a third round of FIT-based CRC screening. We will select individuals in the same target area as in the previous screening rounds, using the electronic database of the regional municipal administration registrations. We will invite all FIT-negatives and all non-participants in previous screening rounds, as well as eligible first time invitees who have moved into the area or have become 50 years of age.

FITs will be analyzed in the special technique laboratory of the Academic Medical Center of the University of Amsterdam. All FIT-positives will be invited for a consultation at the outpatient clinic. In the absence of contra-indications, a colonoscopy will follow at the Academic Medical Center or at the Flevohospital. The primary outcome measures are the participation rate, defined as the proportion of invitees that return a FIT in this third round of FIT-screening, and the diagnostic yield of the program.

**Implications:**

This study will provide precise data on the participation in later FIT screening rounds. This enables to estimate the effectiveness of CRC screening programs that rely on repeated FIT- screening, such as the one that will be implemented in the Netherlands in 2013.

## Background

Colorectal cancer (CRC) is the most common cancer in Europe. In 2008, there were an estimated 436,000 new cases of CRC and 212,000 deaths [1]. Currently, about five percent of persons at average risk develop CRC [2]. The prognosis of patients with CRC is largely influenced by the cancer stage at diagnosis [3]. Timely detection of cancer and removal of its precursor lesions (i.e. adenomas) has been shown to result in a lower CRC incidence and mortality [4,5]. Based on these arguments, screening for CRC meets the Wilson and Jungner criteria for population screening [6].

Several methods are available for population screening for CRC, which can be broadly itemized into stool tests and structural exams [7]. Stool tests include the guaiac, the immunochemical and DNA-marker tests. Structural exams comprise colonoscopy, sigmoidoscopy and CT colonography. The fecal occult blood test (FOBT) and sigmoidoscopy are the only screening methods with a documented mortality reduction over a follow-up period of 10 years. A meta-analysis of FOBT-based screening trials showed a 16% colorectal cancer mortality reduction in FOBT screening after several screening rounds [8]. A large randomized controlled trial in which subjects received either once-only sigmoidoscopy screening or no screening reported a 31% CRC-related mortality reduction in the screening group [9].

The Council of the European Union has recommended population screening for CRC by FOBT [10]. Several EU member states have adopted this advice, although some have implemented non-population based screening programs using other strategies, such as Poland and Germany. In the Netherlands, the effectiveness of FOBT screening has been intensively studied in the past 5 years. Two large randomized controlled trials were performed in the Amsterdam, Nijmegen en Rotterdam region, comparing participation rates of invitational population-based screening using either guiac-FOBT or immunochemical FOBT (FIT) [11,12]. Both trials demonstrated significantly higher participation rates in FIT than in guiac-FOBT based screening: 60% and 62% versus 47% and 50%. In addition, detection rates of advanced neoplasia (CRC and advanced adenomas) were higher in FIT screening than in guiac-based screening: 2.4% and 5.5% versus 1.1% and 1.2%. The effectiveness of population screening is largely determined by the participation rate, not only on participation in the initial screening round, but also on participation in consecutive rounds (“program adherence”). Two years after the first screening round in Amsterdam, 10,265 individuals received an invitation to participate in a second round FIT- screening [13]. Compared to the first round, a significant lower overall participation rate was observed in the second round (43% vs 52%). Overall, 86% of first round participants participated again in the second round and of the previous non-participants, 21% did participate in the second round [14].

Although second round participation in this program was lower, a further decrease is not necessary. In three consecutive screening rounds by guiac-based FOBT screening in Scotland, for example, participation remained stable: 55% participated in a first round, 53% in a second round, and 55% in a third round [15]. Two years after the second round and four years after the first round of FIT screening, members of the same dynamic Amsterdam cohort will once again receive an invitation to participate in population screening by FIT. We will document the level of participation and the yield of screening in this third round of FIT-based screening.

## Methods and design

### Objectives

#### Primary objective

To evaluate the participation rate in and yield of a third round of FIT-based colorectal cancer screening in the Netherlands, two years after the second round and four years after the first round.

### Secondary objectives

We will compare overall participation rates in the third round with those in the first and second round and will compare participation rates in previous participants and non-participants of the first and/or second round. In addition, we will evaluate the complication rate of FIT screening, including follow-up colonoscopy in FIT-positives, and compare these to the results of the first and second round of screening. Also we will evaluate the number and cancer stage of interval cancers in the cohort during the 3 consecutive rounds.

### Study design and population

This study is a designed as a dynamic cohort study. The cohort consists of approximately 11,000 men and women between 50 and 75 years of age at average risk for CRC, living in the Amsterdam region, the same area as in the first and the second round. We will identify cohort members using the electronic database of the regional municipal administration registration (Gemeentelijke Basis Administratie (GBA)).

Institutionalized people will be excluded from participation. Participants in the first or second round who have previously tested positive will not be invited. We will instruct all invitees with rectal blood loss and or change in bowel habits not to participate in screening.

### Invitation procedure

Eligible cohort members will be invited between July 2011 and December 2011. All invitations will be sent out by the regional Comprehensive Cancer Centre Amsterdam using the same centralized invitation program as in previous screening rounds (ICOLON). This institution is also involved in the existing population-based screening programs in the region including breast and cervical cancer screening. Invitees will receive a pre-announcement, followed by an invitation kit 2 weeks later by postal mail containing an invitation letter, an information leaflet, an immunochemical FOBT, a test instruction and a frequently asked questions (FAQ) card. A reminder will be sent two and eight weeks, after the initial invitation.

### Information brochure

The information brochure covers information relevant to colorectal cancer screening. It contains facts on CRC in general, instructions how to perform the FIT, information regarding false-negative and false-positive results, details of the follow-up colonoscopy for FIT-positives, and information on the benefits and harms of screening. This leaflet is an updated version of the leaflet used in the second round. The leaflet is based on the principles of informed-choice, aiming designed to enable all invited persons to make a well-informed decision whether or not to participate.

### Informed consent

An informed consent form is sent together with the FIT. Before analyzing the stool sample, we will check if the informed consent is enclosed and signed. If the informed consent is not correctly available, the stool sample will not be analyzed and the participant will be notified by mail and asked to complete the informed consent.

### FIT

For this study the same FIT as the one used in previous rounds will be used (OC-sensor; Eiken Chimical Co, Tokyo, Japan). This test provides a quantitative measurement of human hemoglobin in stool. The FIT consist of a probe attached to a cap, which fits a collection tube containing hemoglobin stabilizing buffer. Participants are instructed to collect one bowel movement and to sweep the tip of the probe several times through the feces and to insert the probe into the collection tube afterwards. No diet restrictions are advised. In the specialized laboratory of the Academic Medical Center, the returned FITs will be processed using the OC- Sensor - automated instrument. According to previous rounds a subject is considered positive at a cut-off level of 50 ng hemoglobin per milliliter feces.

## Test results

The test result will be sent to the participant and his or her general practitioner by regular mail. In case of a positive test result, the participant will be invited for a consultation at the screening center at the Academic Medical Center in Amsterdam or the Flevo Hospital in Almere. During the consultation, the need for a follow-up colonoscopy will be discussed and the individuals exclusion criteria and/or contra-indications for colonoscopy are checked. Test positive Invitees with end-stage disease and a life-expectancy of less than 5 years, and those who have had a complete colonoscopy in the previous two years, will not be invited for colonosopy. In absence of contra-indications, a colonoscopy will be planned within two weeks after the consultation. In case of a negative test result, no follow up is advised.

### Colonoscopy

Colonoscopies are performed at the Academic Medical Center or at the Flevohospital. All colonoscopies will be performed by experienced endoscopists (≥ 200 colonoscopies) according to the prevailing quality guidelines [16]. Colonoscopy quality indicators will be recorded on a case record form. In case of polyps or cancer, endoscopic removal of the lesions will be attempted during the same procedure. If endoscopic removal is not possible, biopsies will be obtained and histopathological assessment will provide a definitive diagnosis.

### Lesions and pathology

Data on location, size, macroscopic aspect, morphology type of procedure (diagnostic or therapeutic) and endoscopic assessment of radicality will be recorded for all lesions detected during colonoscopy. Lesions will be evaluated by an experienced gastrointestinal pathologist according to the Vienna criteria [17]. All lesions will be classified as adenoma (tubular, tubulovillous, villous), serrated (hyperplastic, sessile serrated adenoma, traditional serrated adenoma), adenocarcinoma or miscellaneous. Dysplasia will be defined as either low-grade or high-grade.

### Follow-up after colonoscopy

Colonoscopy findings will be discussed with the participant by telephone or at the outpatient clinic, if desired, two weeks after the colonoscopy. If the colonoscopy is negative, no follow up is advised. In case of polyps, surveillance colonoscopy is advised according to the Dutch surveillance guidelines [18]. In case of CRC, the patient will be invited at the outpatient clinic and referred to a gastroenterologist or surgeon for further treatment. The general practitioner will be informed about the colonoscopy result by mail.

### Cancer registry

All invitees are linked to The Netherlands Cancer Registry, which collects data of new cancer patients, such as tumor type, incidence date and stage [19]. Using this registry, we can identify interval carcinomas in the three consecutive screening rounds.

### Ethical approval

Ethical approval was obtained from the Dutch Health Council (The Hague, The Netherlands).

### Data analysis

Participation rate is defined as the number of invitees returning a FIT relative to the number of all eligible invitees. The third round participation rate will be compared with those of the two previous screening rounds. Participation rates in subgroups of participants and non-participants of previous screening rounds will be compared. Among third round invitees the following subgroups can be defined: (1) non-participants in the first and the second round; (2) participants in the first and the second round; (3) invitees who participated in the first but did not in the second round; (4) second round participants who did not participate in the first round (5) second round participants who were not invited for the first round (6) second round non-participants who were not invited for the first round and (7) first time invitees. Screening yield is calculated by dividing the total number of participants with detected advanced neoplasia by the number of participants (per-protocol analysis) and the total number of invitees (intention-to-screen analysis). Advanced neoplasia is defined as a CRC or an advanced adenoma. An advanced adenoma is defined as an adenoma ≥ 10 mm, an adenoma with ≥ 25% villous histology or an adenoma with high grade dysplasia. We will express participation rates and diagnostic yield as proportions and present estimates with corresponding confidence intervals. We will compare proportions by Chi-square statistic. We will evaluate the number and stage of interval cancers. Interval cancers will be defined as the proportion of cancer diagnosed in first and second round participants outside the screening. Interval cancers will be identified via cross-linkage of the screening pilot with the Dutch cancer registry. Cancer stage at diagnosis and location will be retrieved via the registry. Descriptive statistics will be used to analyze the interval cancers. Chi-square test statistic will be used to analyze the distribution of cancer stage and location between screen detected cancers of the first, second and third round and interval cancers.

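### The secondary comparison of overall participation between rounds uses a chi-square test that ignores repeat invitees, so it is conservative and can miss small changes

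*Protocol article*

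**What the plan says.** Under Secondary objectives the protocol states: "We will compare overall participation rates in the third round with those in the first and second round". The Data analysis section repeats it: "The third round participation rate will be compared with those of the two previous screening rounds". The only method given there for comparing proportions is "We will compare proportions by Chi-square statistic". No paired, clustered or repeated-measures method is named.

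The rounds share people by design:

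- Background: "members of the same dynamic Amsterdam cohort will once again receive an invitation to participate in population screening by FIT".
- Abstract, Methods and design: "We will invite all FIT-negatives and all non-participants in previous screening rounds, as well as eligible first time invitees".
- Study design and population: "Participants in the first or second round who have previously tested positive will not be invited".

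Six of the seven third-round subgroups in the Data analysis section are defined by whether the person took part in round 2, so their members had been invited before.

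The Background also shows how strongly a person's behaviour carries over: "86% of first round participants participated again in the second round and of the previous non-participants, 21% did participate in the second round".

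**The concern.** An ordinary chi-square test on two overall participation rates assumes that nobody contributes to both. Here many invitees do, and someone who took part before is about four times as likely to take part again (86% against 21%). The variance of the difference between rounds should therefore be reduced by a covariance term, which the stated test omits.

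The Background asks whether participation falls further after round 2 or stays level, and cites Scottish rounds that differed by about 2 points. A test with too large a standard error leans towards reporting no change when the true change is small.

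**Working it through.** The protocol gives no standard error, power or p-value for this comparison, so there is no planned figure to reproduce.

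**Inputs from the protocol.** Round 2 invitees n2 = 10,265 and round 2 participation 43% (Background). Round 3 invitees n3 about 11,000 (Abstract). Re-participation 86% and 21% (Background).

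**Assumptions.** Under no change, both rounds are at 43%. The number m invited in both rounds is 50% to 90% of round 3 invitees. The within-person correlation phi is 0.50 to 0.65. The test is two-sided at 5%. Re-invited people are taken to have the same participation rate as the whole round.

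**Step 1: correlation, rounds 1 to 2.** With p1 the earlier-participant share and p2 = 0.86·p1 + 0.21·(1 − p1), phi = (0.86 − 0.21)·√[p1(1 − p1) / (p2(1 − p2))].

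- p1 = 0.52 gives p2 = 0.548 and phi = 0.65.
- The figures do not recombine directly to the reported 43%. Removal of FIT-positives, new entrants or different denominators may explain this. The share that would give 43% is (0.43 − 0.21)/0.65 = 0.338, with phi = 0.62.

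Use for rounds 2 to 3 is an extrapolation, so the lower limit is set at 0.50.

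**Step 2: independent standard error.** √[0.43·0.57·(1/10,265 + 1/11,000)] = √(4.616×10⁻⁵) = 0.68 points.

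**Step 3: standard error allowing for overlap.** Var = p2q2/n2 + p3q3/n3 − 2·m·phi·√(p2q2·p3q3)/(n2·n3), where p2 and p3 are now the participation rates in rounds 2 and 3.

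For m = 8,800 (80%) and phi = 0.65, the last term is 2·8,800·0.65·0.2451/(10,265·11,000) = 2.483×10⁻⁵. The variance is 4.616×10⁻⁵ − 2.483×10⁻⁵ = 2.133×10⁻⁵, and the standard error is 0.46 points.

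**Step 4: range.** True size is 2·[1 − Φ(1.96 × SE ratio)]. The smallest significant change is 1.96 × the correct standard error; under the stated test it is 1.96 × 0.68 = 1.33 points.

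| Overlap | phi | Correct SE (points) | Variance overstated | True size of 5% test | Smallest significant change (points) |
|---|---|---|---|---|---|
| 50% | 0.50 | 0.59 | 1.35-fold | 2.3% | 1.15 |
| 50% | 0.65 | 0.55 | 1.51-fold | 1.6% | 1.09 |
| 80% | 0.50 | 0.52 | 1.71-fold | 1.0% | 1.02 |
| 80% | 0.65 | 0.46 | 2.16-fold | 0.4% | 0.91 |
| 90% | 0.50 | 0.50 | 1.87-fold | 0.7% | 0.97 |
| 90% | 0.65 | 0.43 | 2.53-fold | 0.2% | 0.84 |

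A simulation of 20,000 data sets per overlap value at phi 0.65 gave type I error of 1.6%, 0.65%, 0.5% and 0.2% at 50%, 70%, 80% and 90% overlap, in line with the formula.

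**Step 5: what a reader would see.** For 43% in round 2 and 44% in round 3, the independent test gives z = 1.47, p = 0.14. At 80% overlap and phi 0.65, z = 2.16, p = 0.03; over the whole range p runs from 0.09 to 0.02. Power for a true 1.5-point change is about 60% with the independent test and about 90% at 80% overlap and phi 0.65.

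**The case against.** The strongest reply is that little depends on this test. That largely stands, and it rules out several stronger readings:

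- **That the primary result is affected.** The primary objective is the participation rate in, and yield of, round 3 itself. These are single-round proportions, and overlap with earlier rounds does not touch them. The between-round comparison is secondary, and no hypothesis, margin or decision rule hangs on its p-value.
- **That the planned confidence intervals are wrong.** The intervals promised are for participation rates and yield as proportions. The protocol does not state an interval for a difference.
- **That false claims of change become more likely.** The omitted covariance is positive, so the error is in the conservative direction. A change as large as the earlier 52% to 43% would be significant either way (z about 13, assuming round 1 had similar numbers).
- **That all chi-square comparisons are unsound.** The seven third-round subgroups contain different people, and chi-square suits them. They also speak directly to adherence by screening history.
- **That half the information is known to be lost.** This holds only towards high overlap and high phi. At 50% overlap and phi 0.50 the variance is overstated 1.35-fold.

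It could also be said that McNemar's test is a chi-square statistic, or that an unseen analysis plan deals with the matter. McNemar is not named, and with people entering and leaving the cohort it cannot compare the overall rates that the objective asks for. An unseen plan may add detail, but the method this protocol names does not fit the design.

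**Conclusion.** The point holds for overall between-round comparisons only. As written, the test overstates the standard error of the difference. For round 3 against round 2 the variance is overstated about 1.3- to 2.5-fold under the stated assumptions. Small changes can be missed, chiefly observed differences of roughly 0.9 to 1.3 points; the lower limit moves between 0.84 and 1.15 with the assumed overlap and phi.

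The direction is secure as long as repeat invitees exist and their participation is positively correlated, and the protocol shows both. The size is less certain, because the overlap share is not given and phi comes from rounds 1 to 2. Round 3 against round 1 was not computed: the round 1 number is not stated, and over four years overlap and correlation may be weaker.

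Severity is moderate: a loss of precision in a secondary comparison, worth correcting before that comparison is run.

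**What to change.** For overall between-round comparisons only, replace the chi-square with an unadjusted binomial GEE or risk-difference model. Use one record per person per round invited, round as a factor, and robust variance clustered on person. Report each difference with its 95% confidence interval. Keep chi-square for groups made up of different people, including the seven third-round subgroups.

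Three additions are optional and should be labelled supplementary. Adjustment for age and sex changes the crude comparison that the objective describes. Clustering on address goes beyond this defect. A McNemar test in people invited to both rounds excludes new entrants and earlier FIT-positives, so it answers a question about a different population.

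The cost is a few sentences of analysis wording. No new data are needed, because forming the seven history subgroups already requires linking each person's records across rounds.

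### The plain chi-square ignores two dependencies: probable co-resident invitees, which make single-round participation intervals slightly too narrow, and re-invited persons, which make round-to-round tests conservative.

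*Protocol article*

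**What the plan says.** The Data analysis section of the protocol article defines the first primary outcome: "Participation rate is defined as the number of invitees returning a FIT relative to the number of all eligible invitees". It says the authors will express participation and yield as proportions and "present estimates with corresponding confidence intervals"; neither the formula nor the confidence level is given. For comparisons it names one method: "We will compare proportions by Chi-square statistic". The comparisons of participation it lists are the third round against each of the two earlier rounds, and subgroups defined by participation history.

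On who is invited, the Abstract (Methods and design) says "a total number of approximately 11,000 average risk individuals (50 to 75 years of age) will be invited" and "We will invite all FIT-negatives and all non-participants in previous screening rounds", together with newly eligible residents. The sampling frame is the population register: "We will identify cohort members using the electronic database of the regional municipal administration registration". Invitation procedure describes a posted pre-announcement, a posted kit and reminders. No rule limits invitations to one person per household, and no section mentions partners, households or addresses.

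On overlap between rounds, Background says that members of the same dynamic cohort are invited again. It reports that 86% of first-round participants and 21% of first-round non-participants took part in the second round, with overall participation of 52% and then 43%.

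**The concern.** An ordinary chi-square test treats every invitee-round as an independent observation, and so does a textbook binomial interval. Two features of the design work against this.

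- **Within a round.** When every eligible man and woman aged 50 to 75 in an area is invited by post, some invitees will live together. Two people at one address receive the same leaflet, kit and reminders and may well decide alike. Positive correlation between them makes a simple interval for one round's participation rate too narrow.
- **Between rounds.** Much of the third-round cohort was also invited in earlier rounds, and past behaviour strongly predicts present behaviour. Two rates measured largely on the same people are positively correlated. An unpaired test ignores that covariance and uses too large a variance for the difference.

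Participation is a primary outcome, and the Abstract's Implications paragraph promises precise data on it for estimating programme effectiveness. The stated precision could therefore be wrong in opposite directions: a little too optimistic for the level in one round, and too pessimistic for the change between rounds.

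**Working it through.** The article gives no sample-size calculation, power or interval width, so there is no figure of its own to reproduce.

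**Inputs from the article.** About 11,000 invitees in round 3 (Abstract); 10,265 in round 2, participation of 52% and 43%, and repeat rates of 86% and 21% (Background).

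**Inputs assumed.** A 95% level; at most two invitees per household; a share *s* of invitees living with another invitee; a within-couple correlation *r* of participation. The article gives neither *s* nor *r*. The working range is *s* = 0.4-0.7 and *r* = 0.3-0.6.

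**Step 1: one round, independence.** Half-width = 1.96 × √(0.43 × 0.57 / 11,000) = 0.93 percentage points.

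**Step 2: one round, household clustering.** Design effect DE = 1 + *s* × *r*. The half-width is multiplied by √DE. Coverage of the nominal 95% interval is 2Φ(1.96/√DE) − 1.

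| *s* | *r* | DE | Half-width (points) | Coverage |
|---|---|---|---|---|
| 0 | – | 1.00 | 0.93 | 95% |
| 0.3 | 0.2 | 1.06 | 0.95 | 94.3% |
| 0.4 | 0.3 | 1.12 | 0.98 | 93.6% |
| 0.5 | 0.5 | 1.25 | 1.03 | 92.0% |
| 0.7 | 0.6 | 1.42 | 1.10 | 90.0% |
| 1.0 | 1.0 | 2.00 | 1.31 | 83.4% |

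The last row is the ceiling for pairs: every invitee has a partner who always decides the same way.

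**Step 3: between rounds, within-person correlation.** Take p₁ = 0.52.

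- Implied second-round rate: 0.86 × 0.52 + 0.21 × 0.48 = 0.548.
- Covariance: (0.86 − 0.21) × 0.52 × 0.48 = 0.162.
- Variances: 0.52 × 0.48 = 0.250 and 0.548 × 0.452 = 0.248.
- Correlation: 0.162 / √(0.250 × 0.248) ≈ 0.65.
- True variance of the difference relative to independence, with full overlap: (0.250 + 0.248 − 2 × 0.162) / (0.250 + 0.248) ≈ 0.35.

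The implied 54.8% is not the reported 43%. The two rounds did not cover one closed group, since test-positives leave and new residents enter. As a check, choose p₁ so that the repeat rates give exactly 43%: p₁ = 0.22/0.65 = 0.338. The correlation is then about 0.62 and the variance ratio about 0.38, so the result hardly moves.

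**Step 4: both dependencies together.** Multiplying by the household design effect, as an approximation that assumes it applies equally to changes: 0.35 × 1.12 ≈ 0.39 and 0.35 × 1.42 ≈ 0.49. Even at DE = 2 the factor is about 0.70, still below 1.

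**Step 5: partial overlap.** With rounds of equal size and overlap *f*, the factor is roughly DE × (1 − 0.65*f*). At DE = 1.42 it falls below 1 once *f* exceeds about 0.46; at DE = 1.12, once *f* exceeds about 0.16.

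**Step 6: effect on a test of round 3 against round 2.** The smallest significant difference under the unpaired test at 43% is 1.96 × √(0.43 × 0.57 × (1/11,000 + 1/10,265)) = 1.33 points. Near full overlap, with the Step 4 factors, the properly computed threshold would be about 1.33 × √0.39 = 0.83 to 1.33 × √0.49 = 0.93 points.

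**The case against.** Much of the case on the other side stands.

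- **The pairing is inferred.** A reader might take it as documented that both partners at an address are invited and decide alike. The article says neither, and it excludes earlier test-positives, so a partner may be absent. Inviting all eligible residents with no one-per-household rule makes co-resident invitees likely, but their share and concordance are unknown.
- **The interval method is not stated.** A reader might infer that the planned intervals ignore clustering. The article does not show this, and an article may leave variance estimation to a fuller plan. What it does fix is the chi-square. The remark on intervals applies only if they are simple binomial ones.
- **The single-round effect is small.** It is 0.05-0.17 points on the working assumptions and under 0.4 points at the ceiling. About ±1 point on 11,000 people is still precise.
- **Large contrasts are safe.** For 52% against 43%, with first-round size assumed between 5,000 and 10,265 because it is not given, z is 10.5-12.9 under independence and still 7.4-9.1 at DE = 2.
- **Overstated significance does not follow.** It is tempting to conclude that household clustering makes small differences look too significant. For round-to-round comparisons the documented dependence works the other way and is larger, so with substantial overlap the test is conservative. For subgroups within round 3, the direction depends on whether partners fall in the same subgroup.
- **Address alone is not a sufficient cluster.** Over four years people move, so a person is not automatically nested in an address.

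These arguments limit the point but do not remove it: the one named test does not suit comparisons between rounds that share many of the same people.

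**Conclusion.** The point holds as a minor one. The named chi-square, and any simple binomial interval, assumes an independence that the design makes doubtful in two ways with opposite effects.

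- **Single-round rates:** intervals are probably slightly too narrow. The half-width is 0.98-1.10 rather than 0.93 points and coverage about 90-94%. This is conditional on 40-70% of invitees being paired and a within-couple correlation of 0.3-0.6.
- **Round-to-round comparisons:** the unpaired test overstates the variance. The true variance is about 0.35 of the independence value, or about 0.4-0.5 with household clustering. This rests on near-full overlap and on the round 1 to 2 repeat rates carrying forward; the article does not state the degree of overlap. The loss is power for small changes, not false positives.

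The second dependence is the better documented, since it rests on the article's own figures. Neither would alter a conclusion about a difference as large as the one already seen between rounds 1 and 2.

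**What to change.** Estimate participation rates and their differences with GEE, or another model with sandwich variance. Cluster on a household identifier fixed once, for example at a person's first invitation, so that each person stays in one cluster across all rounds. Two-way clustering on person and household is an alternative where households change. Take the single-round confidence intervals from this model, and use its Wald test in place of the plain chi-square for comparisons between rounds. State the number of invitees shared by each pair of rounds, so that the reader can see how much the pairing matters.

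The cost is a change of analysis wording and a little more analysis work. No new data collection should be needed, because posted invitations require an address and the repeat rates already reported require person-level linkage between rounds. Single-round intervals become slightly wider; between-round comparisons should become more precise if overlap is substantial.
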